**Assessments**																						
SLEDAI/PGA	x		x	x	x	x	x	x	x	x	x		x	x	x	x	x	x	x	x	x	
SLICC damage score	x														x						x	
QoL questionnaire			x					x			x				x				x		x	
Treatment failure																					x	
Clinical and renal response											x										x	
Autoantibody reduction											x										x	
B cell depletion											x										x	
NET assay			x								x										x	

*S* screening, *B* baseline, *QoL* SF-36 quality of life questionnaire, *FU* follow-up, *SBLA* standard blood laboratory analysis, *Ig* immunoglobulins, *NET* neutrophil extracellular traps

^a^Baseline may be left out if planned within two weeks of screening. ^b^Kidney biopsy only in case of suspected renal involvement

Upon severe flares of SLE disease activity, alternative treatment options will be considered, which can result in the withdrawal of the subject from the study. Patients randomized to the standard-of-care treatment group can cross over to the intervention group in the case of either a severe flare or insufficient treatment response requiring a switch in medication. They will then be considered to have met the primary endpoint of treatment failure, will re-enter the study if they fulfill the inclusion criteria, and receive the complete study treatment of the intervention group as described above.

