### Sample size calculation

The power analysis to determine sample size of the study was based on data from the Synbiose 1 trial (i.e., combination treatment with belimumab and rituximab) and the ALMS trial (i.e., standard of care with mycophenolate and steroids) [32, 38]. To show a significant reduction in treatment failure, we assumed a treatment failure rate during the study period of 104 weeks of 54% in the standard of care group (in accordance with ALMS study results) compared to 23% in the intervention group (in accordance with the Synbiose 1 study results). We calculated that in order to demonstrate a hazard ratio of 2.97 with at least 80% power, using an alpha error confidence level of 5% and beta probability of 0.20, the study would require a total of 70 patients to be randomized with 35 patients in each group.

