### Statistical analysis

The statistical analysis will primarily be performed on the intention-to-treat population. For non-biased immunological endpoints, a per-protocol analysis will be done to assess the pathophysiological effects of adding belimumab and rituximab onto standard of care. The observed rates of treatment failure will be displayed in survival curves and the difference between treatment groups will be assessed using a log-rank test.

Differences in baseline characteristics, immunological endpoints, and clinical response will be explored. The absolute and percentage reduction of autoantibody titers, memory B cells, and NET formation will be analyzed as continuous variables using the non-parametric Mann-Whitney *U* test to compare treatment groups. Clinical disease activity categorized by the aforementioned response criteria will be analyzed using the chi-square test for dichotomized variables. Dosages of immunosuppressants will be analyzed as continuous variables using Mann-Whitney *U* because of the limited number of patients. Missing data will be imputed as that subject’s previously observed value. Patients that have crossed over from the control group to the intervention group will be considered as having met the primary endpoint of treatment failure and will re-enter the study as a new subject. As such, they will be included in the intention-to-treat analysis. Also, they will serve as their own controls in an additional post hoc analysis.

Safety, toxicity, and adverse events will be documented, and the events considered to be at least possibly related to the study treatment will be summarized by severity and treatment group. Infectious AE’s will be presented to an independent infectious disease specialist for evaluation of severity and relation to study participation.

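### Crossed-over controls re-enter the primary intention-to-treat analysis as new subjects, so one person counts twice and the intervention group gains non-randomised records

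*Protocol article*

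**What the plan says.** The Protocol article, Statistical analysis, makes intention-to-treat the primary population and the log-rank test the comparison of treatment failure between groups. It then sets a rule for controls who cross over: they have met the primary endpoint, and they "will re-enter the study as a new subject. As such, they will be included in the intention-to-treat analysis". The next sentence adds a further use of the same patients: "they will serve as their own controls in an additional post hoc analysis".

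Study treatments (the paragraph after Table 2) describes what happens to them. Only control patients may cross over, after a severe flare or an insufficient response that calls for a change of medication. They "will re-enter the study if they fulfill the inclusion criteria, and receive the complete study treatment of the intervention group". No new randomisation and no cap on re-entries is mentioned.

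Sample size calculation rests on randomised patients alone: "the study would require a total of 70 patients to be randomized with 35 patients in each group". It makes no allowance for re-entry records.

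**The concern.** An intention-to-treat comparison counts each randomised patient once, in the arm assigned. The stated rule departs from this in three ways.

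- **Double counting.** The same person is a certain failure in the control arm and a fresh record in the intervention group. The log-rank test treats the two as independent.
- **No randomisation.** The second record is in the intervention group because standard of care failed, not because of allocation. It need not resemble the 35 patients randomised there.
- **An open-label trigger.** Whether a response is insufficient and needs a switch is judged with treatment known. That one judgement produces both a control failure and an extra intervention record.

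What is at stake is the primary result. Its power and error rates would depend on how many controls re-enter and how they then fare, and the design controls neither.

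**Working it through.** **Inputs from Sample size calculation.** Failure by 104 weeks is "54% in the standard of care group" and "23% in the intervention group"; the target is a "hazard ratio of 2.97 with at least 80% power", "using an alpha error confidence level of 5% and beta probability of 0.20". There are 35 patients per group.

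**1. The plan's own figure.**
- Hazard ratio under proportional hazards: ln(1 − 0.54) / ln(1 − 0.23) = 2.97, as stated.
- Schoenfeld events, two-sided 5%, 80% power: 4 × (1.960 + 0.842)² / (ln 2.97)² = 26.5.
- Patients: 26.5 / 0.385 = 68.8, where 0.385 is the mean of 0.54 and 0.23. Rounding up to 27 events gives 27 / 0.385 = 70.1. The stated 70 is reproduced.
- Expected events with 35 + 35: 18.9 + 8.05 = 26.95, giving Schoenfeld power of 80.7%.

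The 70 is therefore sound when each randomised patient is counted once.

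**2. How many records could be added.** Expected control failures are 0.54 × 35 = 18.9. The share that re-enters is not given, so a range is assumed.

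| Share of failing controls re-entering | Added records | Intervention records | Not randomised to it |
|---|---|---|---|
| Quarter | 4.7 | 39.7 | 12% |
| Half | 9.5 | 44.5 | 21% |
| All (ceiling) | 18.9 | 53.9 | 35% |

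**3. Dilution under the planning rates.** The pooled intervention failure rate is (35 × 0.23 + m × r) / (35 + m), where m is the number of added records and r their failure rate (assumed).
- r = 70%: 28.6%, 33.0% and 39.5% for a quarter, half and all, against the planned 23%.
- r = 46%: 25.7%, 27.9% and 31.1%.

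**4. Simulated log-rank test.** Exponential times, two-sided 5%, several thousand trials per cell; repeat runs agree to within about two percentage points. With randomised patients only, power is about 79% and each tail under no effect about 2.5%.

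| Scenario | Quarter | Half | All |
|---|---|---|---|
| 54% vs 23%, re-entrants fail at 70%: power | 63% | 48% | 24% |
| 54% vs 23%, re-entrants fail at 46%: power | 73% | 70% | 62% |
| 54% vs 54%, re-entrants fail at 80%: false harm | 4% | 6% | 11% |

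If re-entrants also fail at 54% under no effect, both tails stay near 2.5%. If they fail at 23% under the planning rates and all re-enter, power rises to about 86% to 87%; this is apparent precision from records that were never randomised.

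**5. Letting failure risk persist within a person.** Here a gamma frailty (assumed) generates the re-entrants' failure rate, and all failing controls re-enter.
- No effect, frailty variance 1: re-entrants fail at about 70%. Total rejection is 6.7%, of which 6.2% falsely favours control.
- No effect, variance 2: re-entrants fail at about 79%. Total rejection is 9.6%, of which 9.5% falsely favours control.
- Planning rates: re-entrants fail at 32% (variance 1) or 37% (variance 2). Power is 80% against 80%, and 78% against 81%.

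So if the treatment works as planned even in re-entrants, the power loss is small. The large losses need re-entrants who respond much less well than the randomised intervention patients.

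**The case against.** **The arm is inferred.** The article never says outright that re-entry records join the intervention arm in the log-rank test. The linking words in the rule could refer back to the failure status, meaning only that crossover patients stay in the analysis as control failures. The sample size, based on 35 randomised per group, fits that reading. It is nevertheless the weaker one. The words that include these patients follow directly on their description as new subjects, and the own-control analysis is introduced as an addition, not a replacement. If the softer meaning was intended, an analyst following the sentence would still build the wrong dataset. An unseen analysis plan may clarify this, but the point concerns a rule the article states, not a detail it leaves out.

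**Full re-entry is a ceiling.** This stands. The primary endpoint includes death, withdrawal and loss to follow-up, after which nobody re-enters. Crossover is optional, limited to flare or insufficient response, and conditional on meeting the inclusion criteria. A reader might infer that about 19 re-entrants, or 35% of the intervention records, are to be expected; the documents do not support that.

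**A bias in favour of the intervention.** A reader might infer serious false-benefit inflation. With all failing controls re-entering and no treatment effect, it reaches about 20% if re-entrants fail at 23% while everyone else fails at 54%. That requires patients selected for failure to do better than others on a treatment that does nothing, and the article offers no mechanism for it. The frailty runs put almost all the inflation the other way.

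**The own-control analysis.** A reader might also object that every re-entrant failed once by selection, so any later failure rate would look like benefit. The article does not say that treatment failure is the outcome of that analysis; autoantibodies, B cells or SLEDAI could be compared instead. Regression to the mean would remain, which is reason to keep it descriptive.

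**Conclusion.** The rule is wrong as written. It puts the same person into the primary analysis twice and adds non-randomised, failure-selected records to the intervention group, so the analysis is not intention-to-treat and the log-rank independence assumption fails. That conclusion rests on the text and needs no simulation.

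The size is uncertain because the article gives neither the re-entry rate nor the re-entrants' failure rate. Over the assumed ranges, power runs from close to its planned level down to about 24%, the lowest value needing both full re-entry and 70% failure. The false-harm rate runs from nominal to about 11%. Inflated false benefit arises only if re-entrants fail less often than randomised patients. All these figures assume exponential times.

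The stated sample size is not in error; the defect lies in the analysis set. It should be corrected before the primary analysis because it decides who is in it.

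**What to change.** Replace the re-entry sentences under Statistical analysis with a definition along these lines:

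- The primary intention-to-treat set is the 70 randomised patients, each counted once, in the randomised arm, with first failure only.
- A control who crosses over is a control failure at the crossover date.
- Records after re-entry form a separate descriptive cohort. They do not enter the primary log-rank test and do not count toward the 70.
- The own-control analysis is descriptive.

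The paragraph after Table 2 should point to this definition, so that re-entry into the study is not read as re-entry into the randomised comparison.

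The cost is a few sentences. No patients, data or procedures are added, access to crossover is unchanged, and the calculation behind the 70 stands, with 26.95 expected events and 80.7% power by Schoenfeld's formula.

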### Trial status

The trial began recruitment in November 2018 and is estimated to be complete in September 2025. The current protocol version is 10 (April 4, 2022).

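### Crossed-over controls re-enter as new subjects within the intention-to-treat analysis; as naturally read, this adds non-randomised intervention records to the primary comparison

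*Protocol article*

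**What the plan says.** Three parts of the protocol article bear on this.

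- **Statistical analysis.** "The statistical analysis will primarily be performed on the intention-to-treat population". For treatment failure, "the difference between treatment groups will be assessed using a log-rank test". Crossed-over controls are scored as having reached the failure endpoint. They then "will re-enter the study as a new subject. As such, they will be included in the intention-to-treat analysis". An own-control post hoc analysis of these patients is described as additional.
- **Study treatments (text after Table 2).** "Patients randomized to the standard-of-care treatment group can cross over to the intervention group in the case of either a severe flare" or an insufficient response that requires a change of medication. They "will re-enter the study if they fulfill the inclusion criteria, and receive the complete study treatment of the intervention group as described above". No second randomisation is mentioned, and no crossover in the other direction is described.
- **Sample size calculation.** The design needs a "total of 70 patients to be randomized with 35 patients in each group", based on failure over 104 weeks of 54% under standard of care and 23% under the combination. Repeat entries are not mentioned.

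**The concern.** An intention-to-treat comparison is protected because chance alone decides who is in each arm and each person counts once. A re-entry record has neither property. It exists only because the patient did badly on standard of care, and its treatment is fixed by the crossover rule. If it enters the log-rank test on the intervention side, the primary estimate mixes the randomised effect with the outcome of selected control failures.

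The resulting hazard ratio would then depend on how many controls cross over and how they fare afterwards. If re-entrants are hard to treat, a real benefit is diluted. If they do better than randomised patients, a benefit can appear where there is none. The clause on re-entry is a positive rule in the text, so this is not a detail left for the analysis plan to supply.

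**Working it through.** **1. The plan's own sample size.** Under constant hazards, the hazard ratio (control relative to intervention) is ln(1 − 0.54) / ln(1 − 0.23) = 2.97, as stated. Schoenfeld's formula, with two-sided 5% alpha (the sidedness is not stated, but two-sided reproduces N) and 80% power, gives

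d = 4 × (1.960 + 0.842)² / (ln 2.97)² = 26.5, rounded up to 27 events.

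The mean failure rate is (0.54 + 0.23)/2 = 0.385, and 27/0.385 = 70.1. The stated 70 is reproduced with each patient counted once.

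**2. How many records could be added.** Expected control failures are 35 × 0.54 = 18.9. The share that re-enters is not given, so I varied it.

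| Control failures re-entering | Added records | Intervention records | Non-randomised share |
|---|---|---|---|
| Half | 9.45 | 44.45 | 21% |
| All | 18.9 | 53.9 | 35% |

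All is an upper bound. Re-entry requires meeting the inclusion criteria, and the composite endpoint also counts death, withdrawal and loss to follow-up.

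**3. Effect on the hazard ratio.** The blended intervention failure rate is (35 × 0.23 + m × p) / (35 + m), where m is the number of added records and p is their 104-week failure risk. The implied hazard ratio is ln(0.46) / ln(1 − blended rate).

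| p | Half re-enter | All re-enter |
|---|---|---|
| 23% | 2.97 | 2.97 |
| 54% | 2.21 | 1.88 |
| 70% | 1.94 | 1.55 |

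For example, with half re-entering at 54%, (8.05 + 9.45 × 0.54)/44.45 = 0.296, and ln(0.46)/ln(0.704) = 2.21.

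**4. Power under the planned effect.** This was simulated with exponential times, a 104-week horizon, 35 randomised per arm, a two-sided 5% log-rank test, and re-entrants added to the intervention arm. With the 70 randomised patients only, power is about 79%.

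| Re-entrant failure risk | Half re-enter | All re-enter |
|---|---|---|
| 23% | about 83% | about 87% |
| 54% | about 63% | about 51% |
| 70% | about 47% | about 23% |

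**5. Error rates with no effect (54% in both arms).** The nominal one-sided rate is 2.5%.

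| Re-entrant failure risk | Direction of error | Half re-enter | All re-enter |
|---|---|---|---|
| 20–30% | favours the combination | 7–12% | 15–22% |
| 54% | favours the combination | near nominal | near nominal |
| 80% | against the combination | 6% | 13% |

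Simulation error is one to two percentage points on power and less on the error rates. Re-entrant times were drawn independently of the person's first record.

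**The case against.** **The milder reading.** The linking words before the intention-to-treat clause could refer to the whole preceding sentence, which begins by scoring crossovers as failures. The patients would then simply stay in the analysis as control failures, which is correct practice. The section never names the arm of the second record. This objection stands in part: a reader might infer that double counting across arms is settled, and the text does not go that far. However, the nearest antecedent is re-entry as a new subject, and the own-control analysis is additional to inclusion, not a substitute for it. The wording therefore permits the wrong analysis even if it was not intended.

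**The bias may be small or harmless.** This also stands in part. If re-entrants fail at the planned 23%, the hazard ratio is unchanged and power rises. If nothing differs between arms and re-entrants also fail at 54%, the error rate is near nominal. The inflated false-positive rates in favour of the combination need selected control failures to do much better than randomised patients under an ineffective regimen, and nothing in the document suggests that. Enrichment with control failures more plausibly works against the combination.

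**Stronger claims the document does not support.**

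- A reader might infer from a completion date "estimated to be complete in September 2025" that late re-entrants would have truncated records that look like successes. That date is an estimate, Table 2 assesses treatment failure at week 104, and the log-rank test censors short follow-up.
- A reader might say the log-rank variance is wrong because one person has two records. Dependence is a fair theoretical point, but these simulations do not model it, so no size can be given.
- A reader might extend the problem to safety denominators. The text ties re-entrants to the intention-to-treat analysis only and defines no safety set.
- A reader might assume re-entrants have had months of prior study treatment. The timing of crossover is not stated.

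**Conclusion.** The rule is wrong as written and should be corrected before analysis. On the natural reading, the primary comparison would no longer be between randomised groups: between a fifth (half re-entering) and a third (all re-entering) of the intervention records could be non-randomised patients selected by failure on control. Power could lie anywhere from about 23% to 87%, against 79% in the randomised patients, and the error rates could move in either direction.

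These ranges rest on constant hazards, on placing the second record in the intervention arm, and on re-entry shares and re-entrant risks that the document does not give. They show sensitivity and do not predict a bias of known sign. The conclusion does not depend on any one cell: the result of a randomised comparison should not turn on who crosses over and how they then fare. If only the milder reading was meant, the text still needs to say so.

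**What to change.** Replace the sentences on crossed-over patients in Statistical analysis with wording such as:

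> The intention-to-treat population is the 70 randomised patients, each counted once in the arm to which they were randomised. A control patient who crosses over is a treatment failure in the control arm on the crossover date. Data after crossover do not enter the randomised between-arm comparisons and are reported separately (own-control analysis and non-randomised extension cohort).

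Add that re-entrants do not count towards the 35 per group, and carry the same definition into the analysis plan.

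The cost is a few sentences. N stays at 70, because the calculation already counts each patient once. No further data are needed, and the crossover option and own-control analysis are unaffected. The only loss is the extra intervention records in the between-arm tests, and these can still be described in full.

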**Methods:**

Synbiose 2 is a phase 3, multicenter, randomized, controlled, open-label 2-year clinical trial. Seventy adults with severe SLE including lupus nephritis will be randomized 1:1 to receive either standard of care consisting of prednisolone and mycophenolate as induction and maintenance treatment, or belimumab and rituximab combined with standard of care as induction treatment, followed by prednisolone and belimumab as maintenance treatment. The primary objective is to assess whether combined B cell therapy will lead to a reduction of treatment failure. Secondary endpoints are complete and partial clinical and renal response and the improvement of SLE-specific autoimmune phenomena. Safety endpoints include the incidence of adverse events, with a special interest in infections.

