## Strengths and limitations of this study

◦ This is a randomized, controlled phase 3 trial with 2 years of follow-up, focusing specifically on patients with severe SLE including lupus nephritis◦ This study’s hypothesis was built on a strong scientific basis of preclinical and clinical studies of belimumab and rituximab used as single agents as well as combined in SLE patients◦ The design includes tapering of mycophenolate and prednisolone as maintenance therapy in the intervention group◦ This study compares two different treatment strategies rather than a single add-on, placebo-controlled agent, which could be perceived as a limitation. However, this set-up is closely related to clinical practice making the outcomes directly translatable to patient care◦ The study is limited by its open-label design

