### Study endpoints

The primary clinical endpoint is the proportion of patients with treatment failure during the trial period, defined as either death, development of end-stage renal disease, major renal or extrarenal flare, sustained doubling of serum creatinine, clinical or renal non-response, requiring induction therapy or plasmapheresis, requiring a dose reduction or discontinuation of mycophenolate—other than established by protocol—for more than 14 or 7 days respectively, discontinuation of belimumab for more than three consecutive doses, inability to complete two rituximab administrations, withdrawal for any reason, or loss to follow-up.

Secondary clinical endpoints will be evaluated at 28 and 104 weeks. Clinical response is defined as a reduction in SLEDAI of ≥ 4 points and no worsening of Physician Global Assessment (PGA) score of > 0.3 points on a scale of 0–3. Other secondary endpoints are clinical remission (defined as meeting the criteria of clinical response and additionally achieving to taper steroids to ≤ 5 mg/day), renal response (complete renal response being < 0,75gr proteinuria per 24 h and a serum creatinine within 125% of baseline), low-level disease activity (SLEDAI ≤ 4 with no activity in major organ systems, hemolytic anemia or gastrointestinal activity and no new disease, PGA ≤ 1 and ≤ 7.5mg prednisolone equivalent), and disease control (SLEDAI ≤ 2 with ≤ 5mg steroids per day) [36]. Patient-reported outcome measure includes the SF-36 Quality of Life questionnaire [37]. Other clinical secondary endpoints are feasibility and safety of combination treatment by monitoring the occurrence of adverse events, with special attention to infections.

The main immunological endpoint is reduction of anti-dsDNA and other disease-specific autoantibodies at 28 weeks, which is also assessed at 104 weeks. Secondary immunological endpoints are reduction of relevant autoantibodies, sustained B cell depletion, and regression of immune complex-mediated excessive NET production at 28 and 104 weeks.

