Monitoring will take place two times a year and the monitoring process will be independent from the investigators. Auditing visits will take place as deemed necessary by the auditing committee. Severe adverse events will be reported to the sponsor within 24 h. A data monitoring committee was not necessary based on the risks of the study. However, to ensure subject safety, safety meetings with independent specialists will be held four times a year in order to monitor and evaluate adverse events, treatment failures, and drop-out. A clinical trial insurance that provides coverage for damage to research subjects through harm caused by the study is available in accordance with the legal requirements in The Netherlands. When medically indicated, trial visits can be intensified as desired or supplemented with the trial’s independent physician in the case of adverse events or harm that occurred during the trial. Additional health care needs that arise during or as a consequence of the trial will be adequately addressed by the investigators.

Several methods are employed to improve participant retention and completion of follow-up, minimizing the burden and practical implications for patients. Scheduling of appointments is planned well ahead of time and reminders are included. Travel allowance will be provided for unplanned visits to the study center. Furthermore, patients who are withdrawn from the study medication will be followed at regularly scheduled study visits as specified by the protocol, unless informed consent is withdrawn. Treatment during the study is defined up to 104 weeks, after which the treatment with belimumab can be continued or patients can be switched to another immunosuppressive regimen as preferred by the treating physician in shared decision with the patient. In the Netherlands, belimumab is covered by insurance companies for the treatment of LN patients posing no barrier to continue any medication from either treatment arm in routine clinical practice after completion of the study.

Significant protocol amendments will be communicated with all relevant parties. We will submit our findings for peer-reviewed, open-access publication, and data resulted from this randomized clinical trial as well as other related documentation will be available on reasonable request. This paper complies with the Standard Protocol Items: Recommendations for Interventional Trials (SPIRIT) recommendations for protocol reporting [39].

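### The only by-arm safety summary fixed in the article is limited to treatment-related events, narrower than the declared adverse-event endpoint and open to attribution bias in an open-label trial

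*Protocol article*

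**What the plan says.** The protocol article states the safety endpoint twice, neither time with a causality condition. The Methods part of the abstract says: "Safety endpoints include the incidence of adverse events, with a special interest in infections". The Study endpoints section lists feasibility and "safety of combination treatment by monitoring the occurrence of adverse events, with special attention to infections".

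The Statistical analysis section first says that safety, toxicity and adverse events will be recorded. It then fixes one summary by arm: "the events considered to be at least possibly related to the study treatment will be summarized by severity and treatment group". It adds one independent step: "Infectious AE’s will be presented to an independent infectious disease specialist for evaluation of severity and relation to study participation".

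On blinding, the list of strengths and limitations concedes: "The study is limited by its open-label design". On oversight, the section on ethical considerations and dissemination says that no data monitoring committee was thought necessary, but that "safety meetings with independent specialists will be held four times a year in order to monitor and evaluate adverse events, treatment failures, and drop-out".

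**The concern.** The endpoint is all adverse events; the summary by arm covers a subset picked by a causality judgement. Randomisation protects a comparison of all events. It does not protect a comparison of events selected after randomisation by an opinion that may be formed with knowledge of the arm.

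The two regimens give good reason to expect attribution to differ. Both arms receive prednisolone and mycophenolate, and the intervention arm also receives belimumab and rituximab. An assessor who knows the allocation may link an event to a new biological more readily than to a familiar drug, or may do the opposite because the background drugs explain the event well enough. The direction cannot be known in advance.

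Comparative safety carries weight in this trial. The Discussion says that the combination might be supported even if efficacy turns out only equal to established treatment, presents the trial as addressing the toxicity of long-term immunosuppression, and hopes to challenge a label restriction that warns against this kind of combination. Readers will want the incidence of all events by arm for those arguments.

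**Working it through.** The article gives no figure for the safety analysis, so there is none to reproduce. The check has two parts.

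**1. The passages side by side**

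| Place in the article | Events covered | Causality condition |
|---|---|---|
| Abstract, Methods | Adverse events, infections of special interest | None |
| Study endpoints | Adverse events, infections given special attention | None |
| Statistical analysis, recording | Safety, toxicity and adverse events | None |
| Statistical analysis, summary by arm | Adverse events | At least possibly related to study treatment |

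The condition appears only where events are compared by arm. It is a rule the article chose to state, so the mismatch does not rest on silence.

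The section names no assessor of relatedness for non-infectious events. For infections it names an independent specialist but does not say that this person is blinded. That specialist also judges relation to taking part in the study, whereas the summary filters on relation to study treatment, so the two judgements are not framed in the same way.

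**2. What a filter can do (illustration)**

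Inputs, all assumed: true incidence p (at most one event per patient, for simplicity) and the share of events attributed to treatment, a_C in the control arm and a_I in the intervention arm.

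Formula: related incidence = p × a. With the same p in both arms, the ratio is (p × a_I) / (p × a_C) = a_I / a_C, whatever p is.

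| True incidence, both arms | a_I vs a_C | Related, intervention vs control | Ratio |
|---|---|---|---|
| 40% | 50% vs 50% | 20% vs 20% | 1.00 |
| 40% | 70% vs 50% | 28% vs 20% | 1.40 |
| 40% | 70% vs 30% | 28% vs 12% | 2.33 |
| 60% | 70% vs 50% | 42% vs 30% | 1.40 |
| 60% | 70% vs 30% | 42% vs 18% | 2.33 |

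The same formula shows how a real difference can vanish. Suppose true incidence is 40% in control and 40% × 1.40 = 56% in intervention. If 70% of control events and 50% of intervention events are attributed, the related incidences are 0.40 × 0.70 = 28% and 0.56 × 0.50 = 28%. The filtered ratio is 1.00 although the true ratio is 1.40.

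A table of all events does not depend on a_I or a_C. This removes attribution bias; it does not remove any effect of open-label treatment on which events are reported in the first place.

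**The case against.** The other side has several fair points.

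- **An all-event table is not ruled out.** The article says that everything is recorded, names one summary, and condenses a fuller protocol. A reader might infer that only related events will ever be reported by arm; the text does not say so. What stands is that the one summary it does fix is narrower than its endpoint.
- **Infections are better protected than other events.** A reader might infer that infections, as the events of special interest, are the most exposed to biased attribution. The documents point the other way: infections are the one category with a named independent assessor of severity and relation. The remaining gap is that blinding of this assessor is not stated.
- **Independent specialists meet four times a year.** This is real oversight of adverse events, treatment failures and drop-out. It serves the safety of participants during the trial and does not change what the final summary contains.
- **Some consequences of toxicity enter the primary endpoint unfiltered.** Death, withdrawal for any reason and off-protocol changes to study drugs count as treatment failure whatever their cause. They are pooled there with flares and non-response, however, and the belimumab and rituximab components can arise only on the intervention regimen. The composite cannot stand in for adverse-event incidence by arm.
- **Study treatment includes standard of care.** The Study treatments section covers prednisolone and mycophenolate, so nothing in the text supports the idea that events on those drugs would be excluded.

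A further reading is tempting: that the plan ignores unequal time on treatment. After all, "Patients randomized to the standard-of-care treatment group can cross over to the intervention group in the case of either a severe flare" or for insufficient response, and such patients re-enter as new subjects. The documents do not support that as an error. No denominator is stated, so crude counts would be inferred from silence, and person-time denominators and the handling of events after crossover are ordinary content for an analysis plan that is not shown. Nor can failure be taken as the end of time at risk: crossover is optional, re-entry requires meeting the inclusion criteria again, and patients taken off study medication keep their scheduled visits.

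**Conclusion.** The point holds for the causality filter alone. The stated summary by arm is narrower than the declared safety endpoint, and it selects events by a judgement that the article does not protect from knowledge of the arm.

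The possible distortion equals the ratio of the attribution shares: 1.40 for 70% vs 50% and 2.33 for 70% vs 30%. These shares are assumptions chosen to show a range. The documents give no basis for estimating them, and the bias could run either way or be absent. The conclusion does not depend on them; it rests on the mismatch between endpoint and summary together with the open-label design. It does not affect the primary analysis or the sample size. The change should be made.

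**What to change.** Rewrite the safety sentence of the Statistical analysis section along these lines:

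> All adverse events, all serious adverse events and all infections will be summarised by severity and treatment group, regardless of causality. Events at least possibly related to study treatment will be shown in a supplementary table.

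If the full protocol or the analysis plan already specifies the all-event tables, it is enough to align the article's wording with them.

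The cost is a sentence and some table shells. No new data are needed, because the section already says that all events are recorded.
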